#### WP2: school implementation

In this work package, the project will estimate the effect of the TREAT INTERACTION school intervention among teachers on implementation and client outcomes in primary schools in Mbale to inform the implementation of child and adolescent mental health services. Specifically, we shall measure the readiness and level of reach of child and adolescent mental health services in Mbale. We shall also determine which implementation strategies are associated with the sustainability of the TREAT INTERACT school training programme in primary schools and the health sector in Mbale.

The quantitative aspects in this work package will be a stepped-wedge cluster randomized trial to randomize 18 schools into six cohorts of three schools. Using the stepped-wedge design will allow every participant to receive the intervention. All cohorts will contribute data throughout 21 months, during both the control and intervention phases. All cohorts will provide data at baseline before any of the schools receive the intervention, at month 0, and then repeatedly every three months adjusted for school terms. Cohort 1 will receive the intervention at month 0; cohort 2 at month 3, cohort 3 at month 6, cohort 4 at month 9, cohort 5 at month 12, and cohort 6 at month 15.

The primary outcomes in this work package will be the effect of task-sharing using the TREAT INTERACT school programme on stigma, mental health literacy, and violence. The 18 schools are systematically selected using STATA and according to two strata: urban or rural location and public or privately owned schools. All teachers will be enrolled for study participation. This will be an open-cohort study where new employees, starting employment after the intervention has been rolled out, will be instructed to complete an information meeting within 4 weeks following their employment, and then take part in the remainder of the data collection. New training courses will be provided to new entrants when needed.

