##### Sample size

Power analyses were conducted in R [47] using the calcPower.SWD function in the samplingDataCRT package and indicated acceptable power, at least 80%, for realistic effect sizes in a stepped wedge design with cluster (school) as a random effect. Longitudinal inclusion of teachers is assumed since it is assumed that most teachers will stay in the schools during follow-up. This model assumes that the within-cluster variance, between-cluster variance and the error variance are equal. Based on the expected sample size of 10 teachers per school, we can expect to detect a treatment effect of 0.2, which is considered a small effect size. However, since preliminary analysis of the situation showed fewer teachers at most schools, a decrease that became apparent during Covid-19, all teachers in the sampled schools will be included in the study.

For the child-caregiver pairs, a sample size of 388 was found sufficient to detect a proportion difference of 0.50 compared to 0.30 with 80% power and 10% loss to follow-up [48]. A stratified sampling proportional to the student population size in each school is used to determine the number of child-caretaker pairs to be included per school. To measure the impact of the intervention among teachers on the community, child-caretaker pairs will be enrolled in a mixed methods design with a nested prospective cohort study to collect quantitative data and conduct focus group discussions and key informant interviews. For the nested prospective cohort, individual study units (child-caretaker pairs) will be selected using systematic sampling. We shall obtain the registration lists of each cohort from the selected primary schools in Mbale. The sampling will start by selecting an element from the list at random (random starting point = P) using computer-generated random numbers. Every K^th^ element in the frame will be selected, where K is the sampling interval. The individuals selected for study enrolment will be done as follows:

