First respondent will have the number = P, 2nd respondent will have the number = P + K, 3rd respondent will have the number = P + K + K. The selection process will be continued until the number of study units (388 child-parent pairs) required per school is attained. At the same time, sex and age-stratified focus group discussions and stakeholder key informant interviews will be employed to collect qualitative data. The mixing of methods aims to establish corroboration of data and will be a concurrent triangulation design.

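### The stop rule for selecting child-caregiver pairs attaches 388 to each school, whereas the sample size calculation and proportional allocation imply 388 over all 18 schools

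*Protocol article*

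**What the plan says.** Three statements in the WP2 Sample size section of the protocol article bear on the number of pairs.

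- The calculation: "For the child-caregiver pairs, a sample size of 388 was found sufficient to detect a proportion difference of 0.50 compared to 0.30". Power is put at 80% and loss to follow-up at 10%.
- The allocation, school by school: "A stratified sampling proportional to the student population size in each school is used to determine the number of child-caretaker pairs".
- The stop rule for systematic sampling from registration lists: "The selection process will be continued until the number of study units (388 child-parent pairs) required per school is attained".

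The WP2 introduction says the trial will "randomize 18 schools into six cohorts of three schools", and the Randomization section confirms that the number of schools is fixed at 18. The sampling interval K is named, but it is given neither a formula nor a value, and no table of school quotas is shown. Nothing elsewhere in the article reconciles the stop rule with the allocation.

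**The concern.** The calculation and the allocation rule together describe one total that is shared out, with larger schools contributing more pairs. The stop rule describes a fixed number reached in each school. They conflict in two ways: in size (388 pairs against 18 times that) and in rule (quotas that vary with school size against one quota for all).

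The size of the child-caregiver cohort, its interview workload and each pupil's chance of selection are at stake. Under proportional allocation every pupil has the same selection probability, 388 / sum(N), where N_s is the number of pupils in school s and the sum runs over the 18 schools. With 388 in every school the probability is 388 / N_s, so pupils in small schools are over-represented unless the analysis weights for it. A reader also cannot tell which target recruitment should later be judged against.

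**Working it through.** **Inputs.** 388 pairs, proportions 0.50 and 0.30, 80% power and 10% loss (Sample size); 18 schools (WP2 introduction, Randomization). Not stated for this calculation, and assumed here: two-sided alpha 0.05, two equal groups, no design effect.

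**1. The article's own figure.** With pooled variance under the null hypothesis, n per group = [1.96 x sqrt(2 x 0.40 x 0.60) + 0.842 x sqrt(0.50 x 0.50 + 0.30 x 0.70)]^2 / 0.20^2 = 93.

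- The total is 2 x 93 = 186. After 10% loss it is 186 / 0.90 = 206.7, so 207.
- With continuity correction it is 206, or 229 after loss.

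The 388 is therefore not reproduced from the stated inputs alone. It is plausible as an overall total with an unstated allowance for clustering:

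- Implied design effect: 388 x 0.90 / 186 = 1.88, or 388 x 0.90 / 206 = 1.70 with continuity correction.
- Average cluster size: 388 / 18 = 21.6.
- Implied intracluster correlation: 0.88 / 20.6 = 0.04, or 0.70 / 20.6 = 0.03.

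Ignoring clustering, 388 in total would give about 97% power after 10% loss. Nothing in the stated inputs calls for 388 in each school.

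**2. The two readings.**

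| | 388 overall | 388 per school |
|---|---|---|
| Pairs in all | 388 | 18 x 388 = 6,984 |
| Pairs per school | 21.6 on average, varying with size | 388 in every school |
| Selection probability in school s | 388 / sum(N) | 388 / N_s |
| Sampling interval K | sum(N) / 388, the same in all schools | N_s / 388, differing by school |

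The ratio of totals is exactly 18. The WP3 Design section lists baseline, six collections and follow-up in parallel with WP2. On that eight-round schedule the readings mean 388 x 8 = 3,104 against 6,984 x 8 = 55,872 pair-visits before attrition.

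**3. Effect on K.** The article gives no school enrolments. As an illustration, assume all 18 schools have equal size N, taken as 800 and as half and one and a half times that.

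| Assumed N | K, 388 per school | Share of pupils taken | K, 388 overall (N / 21.6) |
|---|---|---|---|
| 400 | 400 / 388 = 1.03 | 97% | about 19 |
| 800 | 800 / 388 = 2.1 | 48.5% | about 37 |
| 1,200 | 1,200 / 388 = 3.1 | 32% | about 56 |

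The interval differs 18-fold throughout this equal-size illustration. What the literal rule does to a particular school depends strongly on its enrolment.

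**The case against.** The best defence is that the stop rule refers back to the per-school number already fixed by proportional allocation, and that the bracketed 388 is a misplaced reminder of the overall sample. There would then be one design and one misplaced bracket. This is probably what happened. Even so, the sentence gives 388 for a quantity that averages 21.6, and it is the only place in the selection procedure where a number is given from which K could be set.

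It can also be said that the child-caregiver pairs form a nested cohort. That is right, and it limits the reach of the point: all teachers in the sampled schools are enrolled, so neither the teacher sample nor its power calculation depends on this sentence.

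Three stronger readings are tempting, and the documents do not support them:

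- A reader might infer that 6,984 pairs were planned or are being enrolled. Nothing in the article shows that anyone applied 388 per school.
- A reader might infer that small schools would be sampled almost completely. That follows only at enrolments near 388, and no enrolment is given. At 800 pupils the rule would take about half.
- A reader might infer that 388 is itself miscalculated. It cannot be reproduced here, but alpha and any design effect are unstated, so this does not show that it is wrong.

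A reservation applies on the other side too: the Sample size section never says that 388 is a total. That reading is a strong inference from the single calculation and the proportional allocation.

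**Conclusion.** The Sample size section is wrong as written. Its stop rule attaches 388 to each school, while its calculation and allocation rule imply 388 over 18 schools. The literal difference is 6,984 against 388 pairs. Separately, an equal quota in every school cannot be proportional to school size unless the schools are all equally large, whatever total was intended.

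The 18-fold figure needs only the two stated numbers, 388 and 18. The view that 388 is the overall total rests on inference and is for the authors to confirm. The values of K rest on assumed enrolments. The likely cause is a drafting slip, but it falls in the instruction that selects participants, so it needs correcting.

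**What to change.** Reconcile the stop rule with the calculation and the allocation rule. If 388 is the overall total, replace the sentence with: *Selection continues until the school's proportional quota n_s = 388 x N_s / sum(N) is reached (388 in total over the 18 schools).* Add a table of the 18 quotas, rounded so that they sum to 388.

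Set K from that quota and the list actually used. The article takes registration lists by cohort, and in WP2 a cohort is a group of three schools, so it should say whether the sampling frame is the school list or the cohort list. If 388 per school was really meant, the allocation statement and the justification of the sample size would both have to be rewritten.

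Trial status reports that recruitment began in September 2023, before the article appeared in July 2024. The authors should therefore state which rule and which K were applied in schools already sampled.

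On the overall reading the cost is one sentence, a quota table and a note on past sampling, with no added participants and no change of design.

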##### Randomization

Schools will be identified through a list of schools in the target area, including information on number of learners and teachers, and urban and rural localization. A randomization procedure for school inclusion will be made. Following this, project group members and trained recruiters will recruit the schools. The schools will be sorted into six cohorts randomly incrementally included within 18 months. This design provides within-unit data from the cohorts when they are in a control and intervention condition, and between-unit data between the cohorts in the control versus intervention condition. The procedure used for randomization is stated in detail in an R function. There is no risk of bias when using the R function. Since the number of schools is fixed at 18 there is no need for blocking. As this is cluster randomization, there is no possibility of blinding, and therefore neither concealing.

##### Intervention

The Ugandan-adapted CAMH TREAT INTERACT intervention, inspired by the mhGAP-IG, will be used for the identification, assessment, and management of common mental disorders in children and adolescents whereas the healthcare workers will be trained in the original mhGAP-IG [49]. The clinical decision-tree guides the assessment and differential diagnostic process towards identifying developmental problems (delayed or disrupted development), problems with inattention or hyperactivity (ADHD), conduct disorder (abnormally aggressive, disobedient or defiant behaviour), emotional problems (severe distress, sadness, fearfulness, anxiety or irritability). Examples of typical presentations across different ages and developmental stages are provided to assist the evaluation. Clinicians are also instructed to assess somatic symptoms, home-environment, and school-environment to ensure a comprehensive evaluation. The intervention further details six different protocols for the management of these mental health problems, primarily based on psychosocial and systemic interventions. The described psychosocial interventions can also be provided as general prevention for children with subclinical problems. Lastly, the module guides further follow-up assessment. Experts identified by the Ministry of Health will train trainers who train and follow up teachers and health personnel receiving the intervention.

##### Adherence

To ensure adherence to the intervention, supportive supervision will be given every month for the first three months, then every quarter for the rest of the study period. There will be refresher training every 3rd month after implementation, in line with Ministry of Health guidelines.

##### Outcomes

To be able to compare the two conditions (intervention vs. wait-list), the same variables will be measured before randomization, as well as during and following enrollment to the intervention. To investigate potential gender differences, aggregated information will be separated by gender.

##### Quantitative measures to be collected by each participant group

A detailed supplementary table lists the relevant concepts and chosen scales for documenting the implementation (Supplementary Table 1). In short, we collect data on the school level, teacher and health care level, and child-caretaker level.

##### School level

Children receiving identification, counselling and/or referral for mental health conditions at school: number of home contacts; number of counsellings; and number of referrals. Data will be collected by the appointed mental health focal point teachers at each school and registered into a safely stored book. Data will be registered continuously.

##### Teacher and healthcare level

Data will be collected by trained research assistants every three months. Research assistants will visit each school to collect the data. The following data will be collected:

Measures about the school children: Stigma of child mental health, knowledge about mental health (literacy), personal mental health, attitudes about gender norms, access to suitable MNS services, and use of violence towards school children.Service measures: Access to MNS health services, users treated for MNS disorders, availability of psychosocial interventions, and use of MNS services.Implementation measures: Programme sustainability, leadership, organizational readiness, acceptability, feasibility, fidelity.Reach (scale developed for the current study): Reach refers to the number of children receiving mental health services at each school and the number of referrals and services in health facilities.

Data from healthcare workers will be collected qualitatively after implementation starts.

##### Caregiver level

Data will be collected by trained research assistants every three months. Research assistants will visit each school to collect data individually from each caregiver who agrees to participate. The following data will be collected: Stigma of child mental health, help-seeking behaviour, knowledge about mental health (literacy), discipline, alcohol, and substance use.

##### Child level

Data will be collected by trained research assistants every three months. Research assistants will visit each school to collect data individually from each child whose caregiver has agreed to participate. The following data will be collected: Child mental health, support from teachers, alcohol use, teacher violence, treatment at home (discipline).

##### Data analysis plan

Mean values will be used as summary measures, and mixed effects models will be used to examine the relationships of outcomes with intervention variables and secondarily with other background variables. Background variables will be measured before randomization. Changes between time points are of interest, but changes between the pre- and post-intervention are of particular interest in addition to differences between control and intervention clusters. Based on the repeated measure data, mixed effects analysis will be conducted for outcome variables at the teacher and child level. Mixed effects models are fit to handle any missing data that may occur during data collection under the less restrictive assumption Missing at random. We will use NVivo software for qualitative data analysis when appropriate.

##### Retention

To mitigate both non-retention and non-adherence, once the teachers are enrolled or randomized, the study site will make an effort to follow them for the entire study period. It is projected that the rate of loss-to-follow-up on an annual basis will be at most 5%. Study site staff will develop and implement local standard operating procedures to achieve this level of follow-up.

#### WP3: intersectoral collaboration

##### Primary objective

To implement and evaluate the mhGAP-IG in the health sector while also investigating intersectoral supervision, communication, and referral model between the health and education sector.

##### Specific objectives

(i)To measure the effect of the mhGAP-IG training programme on stigma, mental health literacy, diagnosis, and treatment among health workers in Mbale.(ii)To develop and implement an intersectoral supervision, communication, and referral model between Mbale´s education and health sectors, where teachers have been trained in TREAT INTERACT and the health care providers in the mhGAP-IG.

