##### Design

Data will be collected parallel to the data collection in WP2 (baseline, 6 data collections, follow-up) (Supplementary Table 2).

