##### Measures

Client outcomes (see WP2) will be completed by health personnel. Qualitative interviews (focus groups and key-informant interviews) will be conducted to collect data on client outcomes from health personnel. This data will be collected after start of implementation. Intersectoral collaboration will be measured through referrals, diagnosis, and treatment.

*Reach* and *service outcome* measures will be developed in WP1.

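### WP3 sets out to measure a training effect on health workers' stigma and literacy, but the protocol contradicts itself on whether any baseline or quantitative data on them will exist

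*Protocol article*

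**What the plan says.** WP3, Specific objectives, item (i): "To measure the effect of the mhGAP-IG training programme on stigma, mental health literacy, diagnosis, and treatment among health workers in Mbale".

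Four places describe the data that would serve this objective.

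- **WP2, Teacher and healthcare level.** The section opens with "Data will be collected by trained research assistants every three months". It lists stigma, literacy and other scales, and then "Service measures: Access to MNS health services, users treated for MNS disorders, availability of psychosocial interventions, and use of MNS services". It closes with a sentence on health workers alone: "Data from healthcare workers will be collected qualitatively after implementation starts".
- **WP3, Design.** "Data will be collected parallel to the data collection in WP2 (baseline, 6 data collections, follow-up"; details are referred to Supplementary Table 2, which is not at hand.
- **WP3, Measures.** The first sentence is "Client outcomes (see WP2) will be completed by health personnel". The next introduces focus groups and key-informant interviews with health personnel on client outcomes, followed by "This data will be collected after start of implementation". Referrals, diagnosis and treatment are then named as the measure of intersectoral collaboration.
- **WP3, Procedure.** All permanent clinical staff with child counselling tasks in six level III clinics are to take the 5-day mhGAP course, in two or three rounds. No untrained comparison clinics are described.

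The WP2 Data analysis plan names mixed effects models for the teacher and child levels only. WP4, Procedure, says that impact in clinics will be assessed from the project's referral forms.

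**The concern.** An effect needs something to compare with: a value from before training, or a value from untrained staff at the same time. For stigma and literacy it also needs a score. The sentence that closes the WP2 section on teacher and healthcare measures removes the score and the pre-training value, and WP3 Procedure supplies no untrained group. Field staff who follow that sentence would collect data that cannot answer the objective for these two outcomes.

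The loss would be permanent, because a pre-training value cannot be recovered once the staff have been trained. Evaluating mhGAP in the health sector is the first half of WP3's primary objective, and mhGAP for health care workers is in the study title. A report that presented post-training interviews as a measured effect would mislead its readers.

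**Working it through.** The protocol gives no sample size, power or precision figure for health workers, so there is no figure to reproduce. The check sets the statements side by side.

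**1. Number of rounds.** WP3 Design: 1 baseline + 6 collections + 1 follow-up = 8. WP2: every three months over 21 months from month 0 gives 21/3 + 1 = 8. The two agree, so the WP3 schedule is a coherent plan that mirrors WP2.

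**2. What each statement implies for health workers' stigma and literacy.**

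| Statement | Scored data? | Pre-training value? |
|---|---|---|
| WP3 objective (i): measure the effect | needed | needed, or an untrained group |
| WP2, last sentence on health workers | no | no (0 rounds) |
| WP3 Measures, interviews | no | no |
| WP3 Measures, first sentence | apparently yes | timing not stated |
| WP3 Design | not stated | yes, if it applies to health workers (1 of 8 rounds) |

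The second row cannot stand with the first. It also cannot stand with the last, if the schedule covers health workers.

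**3. Does the schedule cover them?** WP3 participants are teachers, school heads, health personnel, caregivers and children. WP3 Design makes no distinction among them. It could be meant only for the groups shared with WP2, but the text does not say so.

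**4. Does the first sentence of WP3 Measures resolve the conflict?** Not clearly. It concerns client outcomes, which the Trial design section lists as satisfaction, function and symptomatology. Those are not a health worker's own stigma or knowledge. The cross-reference to WP2 could be meant more widely, but WP2 does not define the term.

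**5. Diagnosis and treatment.** Countable sources exist: users treated and service use (WP2), referrals, diagnosis and treatment (WP3 Measures), and project referral forms (WP4). None comes with a stated pre-training count or comparison clinic. Forms created by the project would not be expected to exist before it.

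**6. Result.** If the last WP2 sentence governs, stigma and literacy have no pre-training value, no score and no comparison group, and the effect is not estimable at any number of health workers. If WP3 Design governs, a before-after change is estimable, provided that the scales are given to health workers.

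**The case against.** The strongest reply is that the article also contains the plan it is said to lack. WP3 Design has a baseline, WP3 Measures begins with outcomes that health personnel complete, and the sentence there about timing most naturally refers to the interviews just before it. On that reading only one sentence, in WP2, stands in the way, and the unseen Supplementary Table 2 may show which statement governs. This stands in part. A reader might infer from the WP2 sentence that health-worker data are exclusively qualitative and post-implementation throughout; the documents do not support that as the protocol's only position. The table could settle the intention, but the article's own text would still conflict.

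A reader might also infer that the whole objective is unanswerable. That goes too far. Two of its four outcomes, diagnosis and treatment, have countable sources, even though no contrast is stated for them.

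Nor is the absence of randomised clinics an error. WP3 claims no randomised effect for health workers, and a before-after evaluation is an ordinary design for such a component. The lack of an untrained group matters only because, without it, a pre-training value is indispensable.

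Finally, the analysis plan's silence on a health-worker model is weak evidence, since a fuller analysis plan may cover it.

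**Conclusion.** The point holds as an internal contradiction limited to health workers' stigma and literacy. The stated rule of qualitative collection after implementation starts conflicts with the stated objective and, unless the WP3 schedule excludes health workers, with that schedule; it also sits badly with the opening of WP3 Measures. The number of pre-training rounds for these staff is 0 under one statement and 1, in a total of 8, under the other. Under the first, no effect on either outcome can be estimated.

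For diagnosis and treatment the conclusion is milder: counts will exist, but nothing stated turns them into a measured training effect.

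This rests on the article's text alone. It assumes that the last WP2 sentence means what it says and that no untrained comparison group exists beyond what WP3 Procedure describes. It should be fixed, but it is no more serious than that: it concerns one specific objective of WP3, and WP2's primary outcomes of stigma, literacy and violence among teachers are unaffected.

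**What to change.** Reconcile the WP2 section on teacher and healthcare measures with WP3 Specific objectives, Design and Measures, in one of two ways. The choice depends on whether staff have already been trained. Recruitment began in September 2023 and collection runs to June 2025, but the article gives no dates for the clinic training rounds.

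- **(a) For health workers not yet trained.** Correct the WP2 sentence and WP3 Measures to say that they complete the stigma and literacy scales used for teachers before the course and at the rounds in WP3 Design. Word the objective and report as change from before to after training, not randomised. The cost is a small added questionnaire burden for staff of six clinics and their supervisors, at rounds the protocol already schedules.
- **(b) Where training has taken place without a baseline.** Reword objective (i) as a qualitative exploration for stigma and literacy. Describe diagnosis and treatment as counts from service records and referral forms, and call them a measured training effect only if pre-training counts exist. This costs wording only; the claim becomes weaker but can be supported.

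If some rounds are complete and others are not, state which staff fall under (a) and which under (b). Supplementary Table 2 should be brought into line with whichever text is kept.
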